#### Data management {19}

Castor electronic data capture serves as a clinical data management system, capturing all study data in electronic case report forms (eCRF) conform local METC requirements. To ensure correct data entry, embedded data validation and dependencies are applied and warnings appear in case of data entry outside the reference ranges. Source documents are stored in the trial master file (TMF), investigator site file (ISF) or electronic patient dossier (EPD).

#### Confidentiality {27}

Potential participants are pre-screened through an automatic report function, selecting patients based on pre-specified criteria. Selected participants are approached by their treating physician and only after consent of the patient full access to their EPD is allowed, with subsequent first contact by a research team member. After informed consent, each participant of the study will receive a not reducible, unique study code, which will be used for all study related documents and the eCRF. Except for age, sex, and ethnic group, no other identifying data will be used. The participant identification log is stored separately and only accessible to the coordinating researchers at the concerning study sites and the responsible monitor.

#### Plans for collection, laboratory evaluation, and storage of biological specimens for genetic or molecular analysis in this trial/future use {33}

In case of “biobank” consent additional serum, plasma, whole blood, and 24-h urine samples are collected at baseline and after 24 weeks intervention. This material is frozen at − 80°C and stored for 15 years for future research regarding vascular calcification, inflammation, endothelial dysfunction, and genetics in CKD.

### Statistical methods

#### Statistical methods for primary and secondary outcomes {20a}

Patient characteristics will be presented by treatment arm as mean ± standard deviation (SD) or median with an interquartile range (IQR) for normally and non-normally distributed continuous data, respectively. Categorical variables will be presented as number and percentage. Differences between treatment arms will be visually inspected for clinically relevant differences.

The primary and secondary endpoints will be analyzed with linear mixed models, with repeated measurements (at baseline, 12 weeks, and 24 weeks) and random intercepts at patient level. In case of non-normally distributed residuals of the outcome variables, suitable transformation (e.g., logarithmic) will be performed. Based on the −2 log likelihood evaluation, additional center level and random slopes will be added to the analysis when needed. The main analysis will focus on the three active intervention groups separately, in comparison to the placebo. Also, the additional value of the combined intervention of magnesium citrate and SFOH will be analyzed compared to solely magnesium citrate and SFOH supplementation by coding the magnesium citrate and SFOH as reference category, respectively. Due to stratified randomization, these important confounders are expected to be evenly distributed between the intervention groups. However, confounding by baseline differences of age, sex, eGFR, Kauppila index, baseline plasma magnesium, and phosphate concentrations will be considered in case of clinically relevant or ≥ 10% difference between groups. To evaluate when the effect of the intervention occurs at its maximum, an interaction term for both categorical time variables (12 and 24 weeks versus baseline) will be evaluated in the analysis for primary and secondary outcomes.

The primary and secondary outcomes will be investigated as an ITT analysis. Within the ITT analyses, all participants will be included who have been randomized and participated in the baseline measurements and at least one follow-up visit. This analyses will be based on the initial treatment assignment and not on the treatment eventually received, thus not taking in to account dose alterations or cessation of (part of) the study intervention. Results will be considered statistically significant with a *P*<0.05 (2-sided) for the primary endpoint. For secondary endpoint analyses, we will mainly focus on effect estimates and confidence intervals. Data analysis will be performed in the SPSS 24.0 software for Windows (SPSS incorporated, Chicago, Il, USA) and StataSE 14 (StataCorp, College Station, USA) and will be performed blinded to treatment allocation.

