#### Sample size {14}

The sample size of this study is based on the primary endpoint. A 1.0 m/s difference in PWV is clinically relevant and can be expected with a magnesium intervention of 24 weeks in healthy subjects and a CKD population with accelerated CVD risk [11, 17]. Based on prior studies on arterial stiffness in populations with CKD stages 1–5, with mean PWV values between 10.5 and 12.0 m/s and a standard deviation (SD) of 1.4-3.5 m/s [10, 12, 13], we assume for our study population with an eGFR 15–50 ml/min/1.73m^2^ a SD of 2.0 m/s. With a statistical power of 80%, a two-sided significance of 0.05 and a rho of 0.7 to account for the correlation between baseline and follow-up measurements, 38 participants are required per group. To account for an anticipated drop-out rate of 15% during the 24 weeks, a total of 180 CKD patients will be included and randomized in a ratio of 1:1:1:1, with 45 participants in each intervention group. In case of an unexpected high drop-out rate (> 15%) for reasons not related to study participation (for example starting dialysis, transplantation, referral to a non-participating center), then additional participants can be recruited.

The sample size calculation was performed with the PASS 15.0.5 software and a statistical consultant.

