#### Methods for additional analyses (e.g., subgroup analyses) {20b}

The intervention effect on plasma magnesium and phosphate and their urinary excretion will be analyzed with linear mixed models with repeated measurements and linear regression analysis, respectively. Subgroup sensitivity analyses will be reported for the stratified eGFR, Kauppila index, sex, median age, blood pressure, presence of diabetes, median baseline magnesium, and phosphate levels and proton pump inhibitor or diuretic use to test the robustness of the analysis. In addition, for the primary endpoint of PWV, the mediating effect by plasma magnesium and phosphate levels, blood pressure, T_50-_test, CPPs, α-klotho, and cFGF-23 will be explored using causal mediation analysis.

The analysis of the explorative ^18^F-NaF and ^18^F-FDG PET-scans will be based on the axial regions of interest (ROI). Differences between the intervention groups in standardized uptake value (SUV), target to background ratio (TBR), and most diseased segment (MDS) will be analyzed with linear regression analysis, with adjustment for baseline value.

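### The protocol does not say that the arms share one baseline PWV mean; on its natural reading the primary contrast is a change-score contrast, and a common baseline mean would add precision at no cost

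*Protocol article*

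**What the plan says.** All places are in the protocol article.

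- **Model (Statistical methods {20a}).** The primary and secondary endpoints are analysed with "linear mixed models, with repeated measurements (at baseline, 12 weeks, and 24 weeks) and random intercepts at patient level". Each active arm is compared with placebo. An interaction with categorical time, with baseline as the reference visit, is planned. The covariates considered if imbalanced are age, sex, eGFR, Kauppila index, and baseline magnesium and phosphate; baseline PWV is not among them. The section does not say whether the model contains an arm main effect.
- **Endpoint (Outcomes {12}).** The primary endpoint is the between-group difference in the change of PWV over 24 weeks.
- **Sample size ({14}).** The target is set by "A 1.0 m/s difference in PWV is clinically relevant", with an assumed SD of 2.0 m/s, 80% power, two-sided 0.05 and "a rho of 0.7 to account for the correlation between baseline and follow-up measurements, 38 participants are required per group". Allowing for "an anticipated drop-out rate of 15% during the 24 weeks", participants are "randomized in a ratio of 1:1:1:1, with 45 participants in each intervention group".
- **PET outcomes (Methods for additional analyses {20b}).** These "will be analyzed with linear regression analysis, with adjustment for baseline value".
- **Halfway recalculation (Interim analyses {21b}).** The sample size is recalculated from the observed SD, rho and drop-out; no formula is given.

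**The concern.** When baseline is in the response vector and each arm has its own mean at every visit, the 24-week arm-by-visit contrast with complete data is exactly the difference in mean change. This makes no use of the fact that randomisation gives all arms the same expected baseline PWV. A model that holds the baseline mean common uses that fact and is, in effect, a baseline-adjusted analysis. It is more precise than the change score whenever rho is below 1.

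At stake is precision in a trial with only 38 evaluable participants planned per arm. There is a second consequence: if the halfway recalculation reuses a change-score variance while the analysis is baseline-adjusted, or the reverse, the recalculated number will not match the analysis.

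**Working it through.** **Inputs (Sample size {14}).** Difference 1.0 m/s; SD 2.0 m/s, so SD² = 4; rho 0.7; two-sided 0.05; power 80%; drop-out 15%. The normal quantiles give (1.960 + 0.842)² = 7.849.

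**Step 1: reproduce the plan's figure.**
- Change-score variance: 2 × SD² × (1 − rho) = 2 × 4 × 0.3 = 2.40.
- n per arm: 2 × 7.849 × 2.40 / 1.0² = 37.7, so 38, as stated.
- Drop-out: 38 / 0.85 = 44.7, so 45 per arm and 4 × 45 = 180, as stated.

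Other variances tried with the same inputs do not give 38:
- follow-up value alone: 63
- baseline-adjusted: 33
- change to the mean of the two follow-ups: 29
- baseline-adjusted mean of the two follow-ups: 23
- average of all three visits: 51

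**Step 2: the same trial with a common baseline mean.**
- Variance: SD² × (1 − rho²) = 4 × 0.51 = 2.04.
- Ratio to the change score: 2.04 / 2.40 = 0.85, which is (1 + rho)/2.
- n per arm for 80% power: 2 × 7.849 × 2.04 = 32.0 (just above 32), so 33.

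**Step 3: power at 38 per arm.**

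| | Change score | Common baseline mean |
|---|---|---|
| Contrast variance | 2 × 2.40/38 = 0.1263 | 2 × 2.04/38 = 0.1074 |
| Standard error (m/s) | 0.355 | 0.328 |
| Power for 1.0 m/s, normal approximation | 80.3% | 86.3% |
| Power for 1.0 m/s, t-based | 79.3% | 85.4% |
| Difference detectable with 80% power (m/s) | 2.802 × 0.355 = 1.00 | 2.802 × 0.328 = 0.92 |

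A generalised least squares calculation for four arms and three visits, with the same correlation of 0.7 between all visits, gives the same contrast variances: 0.1263 with arm-specific baseline means and 0.1074 with a common one.

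**Step 4: sensitivity.**

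| rho | Variance cut, (1 − rho)/2 | Power at 38 per arm: change score | Power at 38 per arm: common baseline mean |
|---|---|---|---|
| 0.5 | 25% | 58.7% | 71.1% |
| 0.6 | 20% | 68.3% | 77.8% |
| 0.7 | 15% | 80.3% | 86.3% |
| 0.8 | 10% | 93.1% | 95.3% |

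If 45 per arm start and 7 per arm are seen only to week 12, power at rho 0.7 is 82.1% against 87.1%, a variance ratio of 0.87.

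**The case against.** **The text does not state arm-specific baseline means.** This is correct. Visit and arm-by-visit terms with no arm main effect also fit the {20a} section, and that is the very model recommended here. A reader might infer that the plan has chosen a change-score analysis; the document does not say so. The sample size does not prove it either, because sizing on the change-score variance and then analysing more efficiently is ordinary and conservative. Nor does the absence of baseline PWV from the covariate list, since a model that holds baseline as an outcome would not also list it. The PET regression is a separate analysis in which baseline can only enter as a covariate, so it shows a contrast in approach but no contradiction.

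**The detail may sit in the SAP.** It may, and the SAP is not shown. Silence alone would be no finding. The article does, however, set out the random effects, time coding, reference categories and covariates without signalling a shared baseline mean. The point stands as an improvement to that specification.

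**Nothing is wrong even on the change-score reading.** This also stands. The contrast estimates the stated endpoint, is unbiased under randomisation and meets the planned 80%.

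**Chance imbalance is not an additional harm.** A reader might point to a one-standard-error baseline difference between arms of 45, 2 × √(2/45) = 0.42 m/s, which moves a change-score estimate by 0.42 × (1 − 0.7) = 0.13 m/s, and call this bias. It averages to zero over randomisations and is already inside the standard error. The extra change-score variance, 2.40 − 2.04 = 0.36, is exactly this term: (1 − 0.7)² × 4 = 0.36. Counting it beside the 15% would count it twice.

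**Conclusion.** The point holds as a free gain in efficiency; it does not correct an error. The {20a} section leaves open whether the arms share a baseline mean. The difference-in-change endpoint and the change-score sample size make a change-score contrast the natural reading, but this remains an inference. On that reading, a common baseline mean cuts the variance of the primary contrast by about 15% and raises power from about 80% to about 86% with the same participants. If the investigators already intend a model without an arm main effect, the gain is already present and only needs to be stated.

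The figures rest on SD 2.0 m/s, rho 0.7, equal variances and equal correlation across visits, and 38 complete participants per arm. The gain shrinks as rho rises, and rho is to be re-estimated halfway. The common mean is justified by randomisation. Because the analysis set also requires at least one follow-up visit, it further assumes that early loss does not make the arms differ at baseline.

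**What to change.** In the {20a} section, or in the SAP, write the primary model explicitly:

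- PWV at baseline, week 12 and week 24 as outcomes;
- fixed effects for visit, arm-by-week-12 and arm-by-week-24, with no arm main effect, so that all arms share one baseline mean;
- the arm-by-week-24 term as the primary contrast for each active arm against placebo.

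Use the same form for T50, CPP and the other secondary outcomes measured at all three visits.

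Keep 180 participants and describe the stated 80% power as conservative. For the halfway recalculation, state whether it uses 2 × SD² × (1 − rho) or SD² × (1 − rho²), so that it can be read against the analysis model.

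The cost is a short change to the model specification and one sentence on the recalculation. No new data, visits or software are needed.

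### The random-intercept model with likelihood-selected slopes can misstate the week-12 standard error in either direction and mildly affects week 24; an unstructured covariance avoids this at no cost

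*Protocol article*

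**What the plan says.** Section {20a} of the protocol article puts all three visits, baseline included, into one linear mixed model with "random intercepts at patient level". The structure may then be enlarged: guided by the −2 log likelihood, "additional center level and random slopes will be added to the analysis when needed". Visit-specific effects come from the same model, where "an interaction term for both categorical time variables (12 and 24 weeks versus baseline) will be evaluated" for primary and secondary outcomes, in order to see when the effect is largest. The text names no other within-patient covariance.

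The primary endpoint (Outcomes {12}) is the between-group difference in PWV change over 24 weeks, and the two-sided 5% criterion in {20a} is attached to the primary endpoint. For secondary endpoints the emphasis is on estimates and confidence intervals. The only correlation in the document is in Sample size {14}: "a rho of 0.7 to account for the correlation between baseline and follow-up measurements". No separate values are given for the three pairs of visits.

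**The concern.** A random intercept implies that week 12 and week 24 are exactly as correlated with each other as each is with baseline. If that is untrue, the standard error of a change from baseline is wrong. The plan's only remedy is a random slope admitted by a likelihood evaluation. This raises two difficulties. A slope that is linear in time cannot reproduce every pattern of three correlations. And where the departure is mild, the likelihood step will often leave the slope out.

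At stake are the confidence intervals at weeks 12 and 24 for PWV and for each secondary endpoint measured at all three visits, and the reading of when the effect peaks. In addition, the covariance of the primary model is settled from the trial data although, with three fixed visits, no such choice is needed.

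**Working it through.** **Inputs from Sample size {14}.** SD 2.0 m/s, difference 1.0 m/s, "a two-sided significance of 0.05 and a rho of 0.7", 80% power, 38 evaluable per group, 15% drop-out.

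**Reproducing the plan's figure.** SD of change = 2.0 × √(2 × (1 − 0.7)) = 1.549. n = 2 × (1.960 + 0.842)² × 1.549² / 1.0² = 37.7, so 38. 38 / 0.85 = 44.7, so 45; 4 × 45 = 180. The stated figures reproduce with the change-score variance. (Baseline-adjusted analysis would give 33 and follow-up-only 63.)

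**Assumptions for the check.** Let a, b and c be the baseline–12, 12–24 and baseline–24 correlations. c = 0.7 is the protocol's value; a and b are assumed over a range. SDs are equal across visits unless stated, data are complete, and the means are a full group-by-visit table.

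**Closed forms**, with v = SD² = 4:
- True variance of change: week 12, 2v(1 − a); week 24, 2v(1 − c).
- Random intercept: at both visits the model uses 2v(1 − m), where m = (a + b + c)/3.
- Random intercept plus linear slope, with intercept–slope covariance free and slope variance positive: week 24 is reproduced exactly. At week 12 the model uses v(2 − a − b), that is, the average of the two adjacent change variances. It is right only if a = b.

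**Worked case 0.70/0.85/0.70.** m = 0.75, so the random intercept uses 2 × 4 × 0.25 = 2.0 against a true 2 × 4 × 0.30 = 2.4 at both visits. SE ratio √(2.0/2.4) = 0.913; type I error 2 × (1 − Φ(1.96 × 0.913)) = 7.4%. With the slope, week 12 uses 4 × (2 − 1.55) = 1.8 against 2.4: ratio 0.866, error 9.0%. Week 24 is 1.00. Here the slope makes week 12 worse.

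**Worked case 0.80/0.70/0.70.** True week-12 variance 2 × 4 × 0.20 = 1.6; the slope model uses 4 × (2 − 1.50) = 2.0. Ratio √(2.0/1.6) = 1.118, error 2.8%.

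**Full procedure.** 20,000 simulated null trials per pattern, 38 per arm, slope kept if −2 log likelihood falls by more than 5.99 (2 df, an assumed threshold). Monte Carlo standard error is √(0.05 × 0.95 / 20,000) = 0.15 points. Ratios are model SE / true SE, week 12 then week 24.

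| a / b / c | Intercept only | With linear slope | Slope selected | Error wk 12 | Error wk 24 |
|---|---|---|---|---|---|
| .70/.70/.70 | 1.00, 1.00 | 1.00, 1.00 | 3% | 5.1% | 5.1% |
| .75/.75/.70 | 1.033, 0.943 | 1.00, 1.00 | 25% | 4.8% | 6.2% |
| .80/.80/.70 | 1.080, 0.882 | 1.00, 1.00 | 90% | 5.1% | 5.4% |
| .837/.837/.70 (AR(1)) | 1.131, 0.834 | 1.00, 1.00 | >99% | 5.1% | 5.1% |
| .70/.80/.70 | 0.943, 0.943 | 0.913, 1.00 | 28% | 7.3% | 6.2% |
| .70/.85/.70 | 0.913, 0.913 | 0.866, 1.00 | 64% | 9.0% | 5.8% |
| .75/.85/.70 | 0.966, 0.882 | 0.894, 1.00 | 91% | 7.8% | 5.4% |
| .80/.70/.70 | 1.155, 0.943 | 1.118, 1.00 | 29% | 2.7% | 5.9% |
| .85/.75/.70 | 1.247, 0.882 | 1.155, 1.00 | 92% | 2.2% | 5.4% |

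Other variations are small. With .80/.80/.70 and SDs 2.0/2.1/2.3 the errors are 4.3% (week 12) and 5.2% (week 24). With .65/.65/.70, where no slope variance fits, they are 5.6% and 4.0%. If the slope is taken as independent of the intercept, week 24 is only partly repaired (AR(1): ratio 0.961, error 6.0%).

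An unstructured covariance has a ratio of 1.00 at both visits for every pattern. In a separate simulation of 4,000 replicates its errors were 5.5% (week 12) and 4.8% (week 24) for .70/.85/.70, and 4.9% and 5.1% for .75/.85/.70.

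**The case against.** The other side has four arguments of weight.

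- *The primary test is hardly touched.* The week-24 error stays near 5–6% under the procedure as planned. The larger week-24 figures belong to a random intercept with no slope step, which is not the plan. This stands: a reader might infer that the primary test is invalid, and neither the documents nor the arithmetic support that.
- *Week 12 carries no significance decision.* It serves to locate the peak of the effect. This also stands. The harm there is to the width of intervals, and to the comparison of the two visits, not to a confirmatory claim.
- *The harmful patterns are assumed.* The protocol's single 0.7 is compatible with equal correlations, where the random intercept is exact. Even decay with equal SDs is repaired at week 12 too, and the opposite ordering of the adjacent correlations gives a conservative week 12. This stands as well. A reader might infer that the slope never repairs week 12, or that week-12 standard errors are necessarily too small; both would be wrong.
- *The article does not say that the slopes are linear in time.* Correlated random effects on the two visit indicators would reproduce any 3×3 covariance. That is true, but this reading amounts to an unstructured covariance, so stating it directly loses nothing.

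The likelihood threshold, the slope coding and the degrees-of-freedom method may well be in a document not shown, and their absence is not the point here. The point is the rule the article does state. The rule is also named in advance, and the analysis is to be blinded to allocation, which limits the scope for steering the choice. It does not correct a standard error when the selected structure is the wrong one.

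**Conclusion.** The concern holds in a limited form. The stated rule gives correct standard errors at both visits if the three correlations are equal, and also under even decay with equal SDs provided the slope is selected. If the adjacent correlations differ, the week-12 standard error is wrong even with a linear slope: type I error about 9% at 0.70/0.85/0.70, where the slope model's interval is about 13% too narrow (1 − 0.866), and about 2–3% at 0.80/0.70/0.70, where it is about 12% too wide (1.118 − 1).

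The primary 24-week contrast runs at about 5–6% in the tabulated patterns. It is worst (6.2%) where the departure is mild and the slope is picked only 25–28% of the time. The sample size is not affected.

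These sizes rest on assumed visit correlations, complete data, a linear slope with free intercept–slope covariance, and a 2-df 5% threshold. This is a free improvement to the analysis, not a defect that undermines the primary result.

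**What to change.** In {20a}, replace the patient random intercept and the −2 log likelihood decision on random slopes with a prespecified unstructured 3×3 within-patient covariance over baseline, week 12 and week 24, with a small-sample degrees-of-freedom method. Apply it to PWV and to the secondary endpoints measured at all three visits. The separate question of a centre level is not settled by this change.

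The cost is analysis wording only. The matrix has six parameters, against two for a random intercept and four for an intercept plus correlated slope, and is easily estimated from about 150–180 patients. Both named packages fit it. No new data are needed and the requirement stays at 38 per group. In return, the week-12 and week-24 intervals no longer depend on the correlation pattern, and the within-patient covariance of the primary model is no longer chosen from the trial data.
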